#### Data Analysis

The analysis of the primary outcome, the number of hospitalizations, will be based on a comparison of reimbursement records between the intervention arm and a matched population acting as a control group. Propensity score matching will be used to obtain a comparable control group [14,15] using a large pool of population characteristics (over 100 variables), which include the age at enrollment, gender, geographic location, care level, and presence or absence of common medical conditions. The intervention arm of 500 participants will be compared to an equal-sized matched control group of 500, determined by propensity score matching out of an initial pool of approximately 5000 candidates. Differences between groups will be analyzed through statistical testing, using the binomial rate test for the number of admissions and the t-test for differences in costs.

Analysis of the qualitative data provided by questionnaires will focus on evaluating the participants’ satisfaction with the Sicher Zuhause program overall, and with the individual components such as the case manager interactions and the offered interventions. This will be done through descriptive statistics such as the mean and standard deviations of the satisfaction and helpfulness measured on Likert scales.

The qualitative data will be used to provide insights into to outcomes of the primary objectives and may assist in the improvement of the CareSage predictive model.

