#### Sample Size Calculation

A study with a comparable population by Coleman et al [16] reported a reduction for hospital visits over a 180-day period to 23% in the invention group versus 32% in matched controls. Based on these proportions, 80% power, and a type I error (alpha) of 0.05, at least 386 participants in each group are needed. Accounting for an estimated lost to follow-up of 15%, this increases to at least 454 participants. The sample size for the intervention arm was therefore set at 500.

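### The named tests and the 386 per group make no provision for the propensity matching; if partners' outcomes are positively correlated, cost comparisons lose some precision, while the net error for hospitalizations cannot be settled

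*Protocol article*

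**What the plan says.** The Data Analysis section of the protocol article fixes the design of the comparison: "The intervention arm of 500 participants will be compared to an equal-sized matched control group of 500, determined by propensity score matching", from a pool of about 5000 candidates and over 100 variables, among them age, care level and common medical conditions. The same paragraph names the methods: "Differences between groups will be analyzed through statistical testing, using the binomial rate test for the number of admissions and the t-test for differences in" (the sentence ends with costs).

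The Sample Size Calculation section starts from an external study that "reported a reduction for hospital visits over a 180-day period to 23% in the invention group versus 32% in matched controls". It continues: "Based on these proportions, 80% power, and a type I error (alpha) of 0.05, at least 386 participants in each group are needed". It then allows for loss: "Accounting for an estimated lost to follow-up of 15%, this increases to at least 454 participants". Finally, "The sample size for the intervention arm was therefore set at 500".

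The article mentions no paired method, no standard error that reflects the matching, and no within-pair correlation. It does not write 1:1; that is inferred from 500 against 500. It does not say whether the t-test is paired or unpaired.

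**The concern.** When each control is selected to resemble a participant on predictors of hospital use and cost, the two outcomes in a matched set may be positively correlated. The variance of the difference between groups then contains a term −2·Cov that an independent-samples test leaves out. A binomial rate test between groups is naturally read as a comparison of two independent rates. The t-test is named without a paired form, and the sample size uses no discordance or correlation assumption.

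The article itself makes some positive correlation plausible. Its Introduction reports expenditure 50% higher at ages 65-74 and 100% higher at 75 and over, relative to ages 50-64, and age is one of the matching variables. The hospital-transport model in Risk Score Calculation also uses demographics and medical conditions.

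At stake for costs is precision: intervals wider than necessary, and a test that rejects less often than its nominal 5%. For hospitalizations the question is whether the standard error is right at all, since the planned test reflects neither the matching nor repeat admissions.

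**Working it through.** **1. Reproducing the plan's figure.** Inputs from Sample Size Calculation: p1 = 0.23, p2 = 0.32, power 80%, alpha 0.05. Sidedness is not stated; two-sided reproduces the figure. With the mean proportion p̄ = 0.275 and d = 0.09:

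n = [1.96·√(2p̄(1−p̄)) + 0.842·√(p1(1−p1) + p2(1−p2))]² / d²
= [1.96·√0.39875 + 0.842·√0.3947]² / 0.0081 = (1.2377 + 0.5287)² / 0.0081 = 385.2, so 386.

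This matches the stated 386 and is the independent-groups formula. The other forms tried do not match: 408 with continuity correction, 304 one-sided. For the loss allowance, 386/0.85 = 454.1, against the stated 454; the difference is rounding only.

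**2. What a paired calculation would need.** The documents give no within-pair correlation ρ, so a range is assumed. With Cov = ρ·√(p1(1−p1)p2(1−p2)), the discordant proportion is ψ = p1 + p2 − 2(p1p2 + Cov). The McNemar pairs for 80% power are [1.96√ψ + 0.842√(ψ−d²)]²/d². The true alpha of the unpaired test is 2·[1 − Φ(1.96 × SE ratio)], where the SE ratio is unpaired over paired.

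| Assumed ρ | Pairs needed | SE ratio | True alpha of unpaired test | Power of paired test, 425 pairs |
|---|---|---|---|---|
| −0.05 | 407 | 0.976 | 5.6% | 82% |
| 0 | 388 | 1.000 | 5.0% | 84% |
| 0.05 | 369 | 1.026 | 4.4% | 85% |
| 0.10 | 350 | 1.054 | 3.9% | 87% |
| 0.20 | 312 | 1.117 | 2.8% | 91% |
| 0.30 | 274 | 1.194 | 1.9% | 94% |

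The 425 pairs are 500 × 0.85. The sample size formula gives 84% power at 425 per group. A simulation of correlated binary pairs agreed: the unpaired test rejected under the null in 3.8%, 2.9% and 2.0% of sets at ρ = 0.1, 0.2 and 0.3.

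**3. Costs.** For a continuous outcome with equal variances, the excess interval width is 1/√(1−ρ) − 1: 2.6% at ρ = 0.05, 5.4% at 0.1 and 11.8% at 0.2. For a cost difference with 80% power under independence, unpaired against paired power is 81% v 84% at ρ = 0.1 and 83% v 88% at ρ = 0.2.

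**4. How large could ρ be?** Risk Score Calculation gives an area under the curve of 0.75 for the hospital-transport model. If partners were matched perfectly on a calibrated risk with that discrimination, the binary within-pair correlation would be Var(p)/[p(1−p)]. Assuming normally distributed scores of equal variance in people with and without the event, this is 0.15 at 23% prevalence and 0.17 at 32%, so intervals would be about 8% to 10% too wide. An area of 0.90 gives only 0.44 to 0.47, so ρ = 0.5 needs more than 0.90. That model predicts transport within 30 days, not hospitalization over 8 months, so the bound is indicative. Propensity matching targets enrolment, not outcome risk, which should make ρ lower still.

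**5. Hospitalizations as a count.** Repeat admissions can inflate the variance over what a rate test assumes. With an assumed factor of 1.5 and no pair correlation, the planned standard error is 1/√1.5 = 0.816 of the true one (18% too small), and alpha is about 0.11. Adding ρ = 0.15, the net variance factor is 1.5 × 0.85 = 1.275, and alpha is 2·[1 − Φ(1.96/√1.275)] = 0.083, still above 0.05. With no extra variance and ρ = 0.15, alpha is about 0.034. The direction depends on two quantities that the documents do not give.

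**The case against.** The strongest case is that this is largely a preference of method. Matching on a scalar score makes groups comparable, which is the aim that the article states. Two people with the same score can have quite different profiles, so ρ may be close to zero and the effect negligible. Whether a propensity-matched sample must be analysed as pairs is debated. The t-test is not said to be unpaired, and a condensed article may leave that to a fuller document. Any loss is of efficiency: the simulated power of the unpaired test with 425 pairs was at least 84% at every non-negative ρ examined.

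Most of this stands, and it limits the claim. What remains is that the published text commits to named tests and to a sample size with no provision for the matching. A clustered analysis is valid at any ρ and costs almost nothing.

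Three stronger readings may tempt a reader. One is that the standard errors are simply too large; this needs a positive correlation that the documents do not report. Another is a drastic effect, such as ρ = 0.5 with intervals 41% too wide and a type I error of 0.6%. For a binary outcome the article's own discrimination figure argues against that, and for costs no figure supports it. The third is that the plan is conservative for the primary outcome; calculations with at most one event per person cannot show this for a number of hospitalizations.

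**Conclusion.** The mismatch is in the text: a matched control group, with tests and a sample size that make no provision for matching. It is shown exactly for the 386, is the natural reading of the binomial rate test, and is an unspecified point for the t-test.

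For costs, positive correlation would cost modest precision: intervals about 3% to 12% too wide and a type I error of about 4.4% to 2.8% at an assumed ρ of 0.05 to 0.2, and essentially nothing at ρ near zero. This part creates no bias, excess of false positives or shortage of power. For the number of hospitalizations neither the size nor the direction of the net error is established.

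These figures rest on assumed correlations, on one control per participant as inferred from the equal group sizes, and, for the count outcome, on an assumed variance factor. The point is worth acting on because the remedy is cheap and, for the primary outcome, handles both sources of error together.

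**What to change.** In the Data Analysis section:

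- State that the matched-set identifier is kept in the analysis file.
- For the number of hospitalizations, replace the binomial rate test with a count regression of outcome on group (log link, person-time offset), with robust standard errors clustered on matched set. This allows for within-set covariance and for repeat admissions, and still uses a partner whose match is lost.
- For costs, use a linear model with standard errors clustered on matched set, or a paired t-test.

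In Sample Size Calculation, keep 386 per group. Add that it ignores the matching and, in that respect, is conservative only if the within-pair correlation is positive.

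The cost is a change of wording, one retained variable and slightly more analysis work, with no extra participants or data. If the correlation is near zero, the allowance for matching brings little or no gain.

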### Objectives

The aim of the Sicher Zuhause study—a collaborative effort by Philips, the Techniker Krankenkasse (TK), ServiceCall AG, and the German Red Cross (DRK)—is to evaluate whether the combination of risk scores determined through predictive modeling and targeted interventions offered by a case manager can result in a reduction of hospital admissions and health care costs in a German PERS subscriber population. The primary study aim is to determine whether there is a difference in the number of hospitalizations between the intervention group and the control group over the 8-month intervention period.

In addition, the study aims to assess several secondary outcomes; these are the impact on the number of hospitalizations leading to admissions, the number of days admitted to a hospital, the number of ambulatory visits, the hospital-related costs, and the overall health care costs. Further, qualitative data collected through questionnaires will be used to assess the participants’ satisfaction with the PERS devices used in the study and with the Sicher Zuhause program as a whole.

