## Discussion

This protocol describes a study that aims to determine if the combination of risk scores determined through predictive modeling and interventions offered by a case manager can result in a reduction of hospital admissions and health care costs in a German PERS subscriber population. The rapidly aging population with multiple comorbidities presents numerous challenges to effective care management, and therefore, alternatives to hospital and institutional care are needed to optimize health care costs and improve patient outcomes [17]. In the future, the results of this study can lead to better health outcomes for the population described.

This study has a few limitations. First, it does not include a randomized design, and the use of a retrospective control group may lead to selection bias. In the study, this concern is partially addressed by the use of propensity score matching. Second, the effect of the risk prediction and the interventions cannot be easily separated. As such, the study aims to evaluate the combination of the two, where the predictive model helps to identify the right subset of participants to whom interventions should be offered. Further, analysis of the qualitative data can help to provide insights into the performance of the predictive model and the effectiveness of the interventions. Another option would be to include additional study arms; however, due to the expected recruitment rate, this is likely not feasible.

A third limitation is that it might be difficult to capture data on health care utilization that may be initiated outside of the PERS service. Capturing emergency department visits and hospitalizations is important because the study population is a high health care utilization group that is at risk for emergency transport, and patients are typically taken to the nearest medical center for emergency care services. However, self-reported data from patients may help mitigate some of these challenges.

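### The binomial rate test, applied to total hospitalizations, treats repeat events in one person as independent and so exceeds its 5% type I error when individual risk differs

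*Protocol article*

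**What the plan says.** The Objectives section sets the primary aim as determining "whether there is a difference in the number of hospitalizations between the intervention group and the control group over the 8-month intervention period". The Data Analysis section repeats this: "The analysis of the primary outcome, the number of hospitalizations, will be based on a comparison of reimbursement records". The groups are of equal size: "The intervention arm of 500 participants will be compared to an equal-sized matched control group of 500". Differences are then to be tested "using the binomial rate test for the number of admissions and the t-test for differences in costs". No sentence limits the count to a first event or to one event per person.

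The Sample Size Calculation section works with proportions of people. The cited study "reported a reduction for hospital visits over a 180-day period to 23% in the invention group versus 32% in matched controls", and the article continues: "Based on these proportions, 80% power, and a type I error (alpha) of 0.05, at least 386 participants in each group are needed".

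Two further statements bear on whether people share one rate. The Discussion says that "the study population is a high health care utilization group that is at risk for emergency transport". The Risk Score Calculation section describes a model that ranks participants by their risk of hospital transport (area under the curve 0.75) and expresses each score relative to the average.

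**The concern.** A binomial rate test on two event totals conditions on the overall number of events and asks whether the split between the groups fits a fair coin. That is valid if each event is an independent draw and everyone has the same event rate. Hospitalizations in frail elderly people are unlikely to meet either condition: one person can contribute several, and some people carry much more risk than others. The intervention itself presumes the second point, since a risk score is useful only if risk differs.

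When risk differs, the totals vary more than the test allows. The p-value is then too small, and the study would report a difference in hospitalizations more often than 5% of the time when there is none. This is the primary analysis of a non-randomised comparison that already carries an acknowledged risk of selection bias.

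**Working it through.** **1. The article's own figure.** With 32% v 23%, two-sided alpha 0.05, 80% power and pooled proportion 0.275:

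n = [1.960·√(2·0.275·0.725) + 0.842·√(0.32·0.68 + 0.23·0.77)]² / 0.09² = 385.2, so 386 per group, as stated. Allowing for 15% loss, 386/0.85 = 454.1, which agrees with the stated 454. The arithmetic is sound. It is a calculation with one yes/no result per person, whereas the stated outcome is a count.

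**2. Inputs for the type I error of the named test on totals.**
- From the article: 500 per group, alpha 0.05 and 32% with an event in 180 days.
- Assumed: no true effect, 8 months = 243 days, and negative binomial counts per person with dispersion k, where k = 0 means a common Poisson rate for everyone. The article gives no mean, variance or repeat-admission figure, so k is shown as a range.

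**3. Formulas.**
- 180-day mean from P(no event) = 0.68: μ₁₈₀ = (0.68^(−k) − 1)/k, or −ln 0.68 at k = 0.
- 8-month mean: μ = μ₁₈₀ × 243/180.
- Variance/mean ratio: φ = 1 + kμ.
- The test assumes that the difference in totals has variance 2·500·μ, but the true variance is φ times that. Approximate type I error is therefore 2·[1 − Φ(1.96/√φ)].

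**4. Results.** The last column is a simulation of the exact conditional test.

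| k (assumed) | μ₁₈₀ | μ, 8 months | φ | √φ | Formula | Simulated |
|---|---|---|---|---|---|---|
| 0 | 0.386 | 0.521 | 1.00 | 1.00 | 5.0% | 4.6% |
| 0.1 | 0.393 | 0.531 | 1.05 | 1.03 | 5.6% | 5.4% |
| 0.25 | 0.405 | 0.547 | 1.14 | 1.07 | 6.6% | 6.0% |
| 0.5 | 0.425 | 0.574 | 1.29 | 1.13 | 8.4% | 7.5% |
| 1 | 0.471 | 0.635 | 1.64 | 1.28 | 12.5% | 11.6% |
| 2 | 0.581 | 0.785 | 2.57 | 1.60 | 22.1% | 21.6% |

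Repeat simulations differ from these by a few tenths of a percentage point. The exact test is slightly conservative, which is why it starts below 5% and is still close to 5% at k = 0.1. The column √φ is the factor by which the true standard error exceeds the assumed one.

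**5. Effect of matching.** A positive correlation ρ between the counts of matched partners reduces the true variance to φ(1 − ρ) times the assumed one. The excess is cancelled at ρ = 1 − 1/φ, that is 0.12, 0.22, 0.39 and 0.61 for k = 0.25, 0.5, 1 and 2. The article states no such correlation.

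**6. The alternatives.** In 4,000 simulations each at k = 0.5, 1 and 2 (using the 180-day mean), a rate difference with a between-person variance had type I error of 4.7% to 4.9%. A test of the proportion with at least one hospitalization had 4.7% to 5.4%.

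**The case against.** The strongest reply is that the article gives no formula or counting rule for its test, and that the one place where it handles the outcome numerically treats it as a proportion of people. Read that way, the test holds its 5%. This stands as a possible reading, and it is why the type I error result is conditional. It does not rescue the text: a proportion with at least one hospitalization is not the number of hospitalizations named as the primary outcome.

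A second reply is that the test is named for admissions, while the Objectives list hospitalizations leading to admissions as a separate secondary outcome. The wording is loose. But the Data Analysis section opens with the number of hospitalizations as primary and offers only this one test for a count.

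Third, the size of the excess rests on an undocumented k, and small values do little harm. That is correct. The area under the curve does not supply k either, since it describes 30-day prediction in a development set of deceased subscribers.

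A reader might also infer three further faults that the documents do not support:
- That the planned primary confidence interval is too narrow. The article specifies no interval for the primary outcome.
- That time at risk and the matched pairs will be ignored. A condensed article may leave both to an analysis plan that is not shown.
- That the t-test for costs is invalid. Nothing here demonstrates a fault in it with 500 per group.

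**Conclusion.** The point holds in conditional form. The article itself fixes both a count outcome and a test that, on totals, is valid only for independent events at a common rate, and its own premise of differing individual risk contradicts that. The direction of the error is clear unless within-pair correlation is strong enough to cancel it. The size is not known: about 6% to 22% instead of 5% for k from 0.25 to 2, and close to 5% for k of 0.1 or less, before any offset from matching. It would go too far to say that the study will exceed 5% by a known amount, because neither k nor the intended unit of analysis is stated. Under the proportion reading type I error is about 5%, but the declared outcome goes unanalysed. On either reading the text needs changing.

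**What to change.** State whether the primary analysis counts all hospitalizations or people with at least one.

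- **If all hospitalizations:** replace the binomial rate test with a person-level count model, either negative binomial or quasi-Poisson, with robust standard errors. Use log days at risk as offset and allow for the matching, for example by clustering on the matched pair. Report the rate ratio with 95% CI, and restate the sample size for a count.
- **If people with at least one:** restate the primary outcome as that proportion wherever it appears, so that outcome, test and sample size agree.

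The cost analysis can stay as it is.

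The cost is a sentence or two in the article and minor programming. Reimbursement records are already the planned data source. The interval from a count model will be wider than one based on the Poisson variance, by about √φ before any gain from matching. Power should be rechecked. As an illustration with rate ratio 23/32, n = (1.960 + 0.842)²·(1/μ₁ + 1/μ₂ + 2k)/[ln(23/32)]², where μ₁ is the control mean and μ₂ = μ₁·23/32. At k = 1 this gives 510 per group on 180-day means and 415 on 8-month means, before loss to follow-up, against the stated 386.

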#### Sample Size Calculation

A study with a comparable population by Coleman et al [16] reported a reduction for hospital visits over a 180-day period to 23% in the invention group versus 32% in matched controls. Based on these proportions, 80% power, and a type I error (alpha) of 0.05, at least 386 participants in each group are needed. Accounting for an estimated lost to follow-up of 15%, this increases to at least 454 participants. The sample size for the intervention arm was therefore set at 500.

#### Ethical Considerations

The Sicher Zuhause study will be conducted in accordance with the most recent version of the Declaration of Helsinki. The study has been assessed and approved by the internal board of ethics of Philips Research (Internal Committee of Biomedical Experiments), and has been reviewed and approved by the Western Institutional Review Board (WIRB, tracking number 20182221).

All data collected in the study will be maintained in compliance with the General Data Protection Regulation privacy directive and the German data protection law. Data will be pseudonymized where possible and kept encrypted both in transit and at rest.

